###### Secondary outcomes

2.1.5.1.2

GPS-derived mobility-related activities, including maximum distance traveled from home (km), daily step count (steps/day), and area of the convex hull [km^2^] (i.e., the minimum bounding geometry enclosing all the GPS loggings for each participant and the maximum area in which the participant engaged in activities), and GPS-derived quantity of out-of-home activities including number of trips (to out of home locations), homestay ratio (%), and time out of home (minutes) will be measured using smartwatch GPS data (40).

Secondary outcomes related to measure community mobility, self-reported physical activity, health and social service use, health behaviors, health status, quality of life, and community belonging will be collected via telephone interviews by trained research assistants using structured surveys. This includes self-reported health and social services utilization, including number of emergency department visits, number of hospitalizations, number of physician visits (general practitioner or specialist), number of visits with nursing or allied health professional (e.g., nurse, dietitian, pharmacist, physiotherapist, psychologist, counseling) and number of times community-based services used categorized by service (e.g., homemaker, meal service, adult day program) will be collected using the Health and Social Service Utilization Index (adapted for relevance to EMBOLDEN (41, 42)). We will also measure self-reported physical activity (Physical Activity Scale for the Elderly; PASE (43), community mobility (Life Space Assessment; LSA (44–46)), nutritional risk (Seniors in the Community: Risk Evaluation for Eating and Nutrition, Version II; SCREEN-II (47)), health-related quality of life (12-Item Short Form Survey; SF-12 (48) and EQ-5D-5L (49), resilience (Short Form 5-item Resilience Scale (50)), loneliness (6-item De Jong Gierveld Loneliness scale (51), physical activity literacy (Outcome Expectations for Exercise (OEE) scale (52, 53), depression (Patient Health Questionnaire-9; PHQ-9) (54), sense of community belonging, a measure of social capital at the neighborhood level (55), collective capacity within an individual’s social network (Collective Efficacy of Networks questionnaire; CENS (56)), food security (57), knowledge of chronic disease risk factors related to physical activity and healthy eating (Health and Behavior Assessment Tool; HABiT (58)), and food literacy (Short Food Literacy Questionnaire; SFLQ (59)).

These outcomes were selected recognizing the multi-faceted nature of the EMBOLDEN intervention and key areas it was intended to impact. Many of the above secondary outcomes have tools to capture the relevant data and guidelines for calculating total and/or subscale scores. The average completion time for secondary outcomes was 47.7 min (45–51) minutes based on pilot testing with older adult Strategic Guiding Council members (*n* = 3).

##### Implementation outcomes

2.1.5.2

The selection of implementation outcomes was guided by the *Reach Effectiveness Adoption Implementation Maintenance (RE-AIM) framework* (60). This framework has been used to guide the planning and evaluation of health-related interventions from efficacy trials to implementation interventions (61). A definition of each item within the RE-AIM framework, along with the relevant EMBOLDEN measures, timing of data collection, and data sources, are provided in Table 1. Implementation outcomes for most framework domains include both quantitative and qualitative data. The “E” in the RE-AIM framework refers to effectiveness; thus, these outcomes (cited in Section 2.1.5.1 above) are also included in Table 1.

**Table 1 tab1:** Alignment of EMBOLDEN outcomes with RE-AIM framework.

RE-AIM outcome domain (58)	Measure	Data collection timepoint^a^	Data source (see data collection section for details)
R (Reach, Participant level)	-# Potential participants interested -# Eligible participants in the catchment area (by neighborhood using 2016 and 2021 census data)	t_1_	Recruitment Logs
	-# and % participants eligible (including demographics) -# Participants recruited by recruitment method	t_1_	Screening Logs
	-reasons for ineligibility	t_1_	Screening Logs
	-# and % participants enrolled (including demographics)	t_1_	Screening Logs
	-# and % participants retained (including demographics)	t_1_, t_2_, t_3_	Participant database
	-Reasons for dropout	t_1_, t_2_, t_3_	Exit survey
	-Representativeness of sample reached	t_3_	Census data
E (Effectiveness, Participant level)	-See Section 2.1.5.1 for a description of primary and secondary outcomes	t_1_, t_2_, t_3_	Participant Data Collection
	-Attendance—weekly group-based education sessions	t_2_	Group Session Attendance Logs
	-Completion of facilitated system navigation sessions	t_2_	System Navigation Attendance Logs
	-Satisfaction and perceived impacts - group-based sessions	t_3_	Mid and end of study survey (all intervention participants) Interviews (subset of intervention participants)
	-Satisfaction and perceived impacts – system navigation	t_3_	Interviews (subset of intervention participants)
	-Awareness of community programs/resources	t_3_	Interviews (subset of intervention participants)
	-Utilization of community programs/resources	t_1_, t_2_, t_3_ t_3_ up to 3 (start, mid- and end of group-based program)	End of study survey (all intervention participants) Interviews (subset of intervention participants) Genie® (intervention participants)
	-Social network analysis variables (e.g., size of the network, diversity of the network, number of strong/weak ties, number of hobby or community groups).	t_1_, t_2_, t_3_	Genie® (intervention participants)
Adoption (Organization level)	-# and % of community partners approached that join Strategic Guiding Council (SGC)	t_1_, t_2_, t_3_	SGC Recruitment Logs
	-Reasons for non-participation in SGC	t_1_, t_2_, t_3_	SGC Recruitment Logs
	-# and % of community partners retained in SGC	t_2_, t_3_	SGC Recruitment Logs
	-Reasons for discontinuation on SGC	t_2_, t_3_	SGC Recruitment Logs
	# and % of community partners approached and joined Community Advisory Board (CAB)	t_1_, t_2_, t_3_	CAB Recruitment Logs
	-Reasons for non-participation on CAB	t_1_, t_2_, t_3_	CAB Recruitment Logs
	-# and % of community partners retained in CAB	t_2_, t_3_	CAB Recruitment Logs
	-Reasons for discontinuation on CAB	t_2_, t_3_	CAB Recruitment Logs
	-# Community partners who agree to participate in intervention delivery among those approached	t_1_, t_2_, t_3_	CAB Recruitment Logs
	-# Trained interventionists within each neighborhood	t_1_, t_2_, t_3_	CAB Recruitment Logs
I (Implementation, organization level)	-Fidelity of delivery (% of core content delivered in group-based intervention sessions, content delivered during system navigation sessions)	t_2_	Group Session Checklist
	-Adaptations at local sites	t_1_, t_2_	Research Team Meetings with Interventionists (notes)
	-Barriers and facilitators to implementation	t_2_, t_3_	Research Team Meetings (notes) and Focus Groups with Interventionists (transcripts of audio-recordings) Interviews (intervention participants) CAB, SGC Meeting Notes
	-Cost of delivery (per participant, group, site)	t_1_, t_2_	Study Budget
M (Maintenance. Organization level)	-# Community partners intending to offer the program 3 months after study discontinuation^b^ ^−^Reasons for program cessation	t_3_	Key informant interviews

a t_1_ = baseline, beginning of study; t_2_ = 3 months, post-intervention; t_3_ = 6 months, end of study.

b The timeframe for assessing maintenance in RE-AIM is 6 months post-intervention. We adjusted the timeframe to 3 months to align with our final data collection timepoint (t_3_).

#### Participant timeline

2.1.6

A number of activities will be conducted approximately 2 weeks prior to the beginning of the intervention (t_1_), including eligibility screening, informed consent, collection of demographic data, the first 7-day period for wearing the smartwatch, and randomization (performed after demographic data are collected and the participant has returned smartwatch after the first 7-day wear period). Time point t_1_ marks the beginning of the 3-month intervention period. Table 2 provides the details regarding the schedule for screening, wearing of the smartwatch, randomization, and assessments for participants. The intervention is designed for participants to start as a group and engage in the series of group-based sessions together.

**Table 2 tab2:** Timeline for EMBOLDEN participant screening, enrolment, and assessments.

Activity/assessment	Screening, informed consent, data collected prior to start of intervention t0	Baseline (start of intervention) t_1_	Follow-up post-intervention 3 months t_2_	Follow-up 6 months after baseline t_3_
Eligibility screen	X			
Informed consent	X			
Demographics, CaMos Frailty Index, GAQ, COVID-19 status^a^	X			
Randomization	X			
Smartwatch (worn 7-days *prior* to t_1,_ t_2_ and t_3_)	X		X	X
Primary Outcome: MVPA (minutes/day)		X	X	X
Secondary Outcomes: GPS-based mobility-related and out-of-home activities, PHQ9, LSA, Food Security, SCREEN II, SF-12, PASE, EQ-5D-5L, De Jong Gierveld, RS-5, CENS, Sense of Community Belonging, HABiT, OEE, SFLQ, Health and social services use^b^		X	X	X
EMBOLDEN program satisfaction survey			(also, mid-point or 1.5 months) X	

a Canadian Multicenter Osteoporosis Study (CaMos) collected to describe population at baseline (92), Get Active Questionnaire (GAQ).

b Patient Health Questionnaire-9 (PHQ9), Physical Activity Scale for the Elderly (PASE), Life Space Assessment (LSA), Seniors in the community: risk evaluation for eating and nutrition, Version II (SCREEN-II), 12-Item Short Form Survey (SF-12), Shortened Form 5-item Resilience Scale (RS-5), Collective Efficacy of Networks questionnaire (CENS), Health and Behavior Assessment (HABiT), Outcome Expectations for Exercise (OEE), Short Food Literacy Questionnaire (SFLQ), adapted Health and Social Services Utilization Index (HSSUI).

#### Sample size

2.1.7

The results of the pilot study suggested a sample size of 250–500 for this trial (all sites) (33). The sample size calculation was based on the effect size for the primary outcome measure (MVPA) and appropriateness for the statistical model used to analyze the trial data (62). The following two-pronged approach was used to acknowledge the uncertainty in the pilot trial estimate of effect: (1) eliciting MVPA effect sizes from other relevant published studies, and (2) calculating the sample size for various plausible values of key parameters in the calculation using values from the pilot augmented by estimates from other published studies (63). A literature review identified two recent systematic reviews for interventions promoting physical activity: Wright et al. (64) and Larsen et al. (65). The review by Wright et al. (64) was most useful because of their comprehensive reach (included 2,762 trials), use of MVPA variance estimates based on survey data from 5 cycles (2007–2017) of the Canadian Health Measures Survey (*n* = 13,173 respondents age 18–79) (66); and breakdown of MVPA effect sizes by distributional anchors (e.g., 25th/50th/75th percentiles), different populations (e.g., older adults), and follow-up periods (e.g., 3+/6+/12+ months).

The following parameters were fixed in all sample size calculations: *α* = 0.05, two-sided hypotheses, power = 0.80, and attrition (90% retention at 3 months and 80% at 6 months as per pilot results). The *total* sample size ranged from 190 to 1,074, depending primarily on the assumptions regarding effect size and variance. Despite this wide range, the positive qualitative feedback from intervention participants suggested that the higher effect size seen in the pilot may be realized, thus leading to the final estimated range for the sample size of 250–500 (~50 per site).

#### Recruitment and retention

2.1.8

Multiple methods will be employed to recruit and retain participants, with modalities, approaches, and messages that may attract a general older adult population based on existing literature and input from our SGC. Recruitment will begin by confirming the boundaries for the study neighborhoods since census tracts may not truly correspond to residents’ perceptions of their neighborhood. Engaging CABs who are well-informed about the local context will be instrumental to help the team develop effective recruitment and engagement strategies and local assets, understand and gaps/needs. In Hamilton census tracts the population size is typically 3,000–4,000 residents, with approximately 30% of the population over 55. Thus, the average neighborhood size to recruit from is 900 to 1,200 individuals. The two Toronto neighborhoods have 31,600 and 13,770 residents, with both having approximately 23% of the population over the age of 55, with 7,200 and 3,200 individuals available for recruitment, respectively.

Existing community organizational structures will be leveraged to attract and engage participants in each neighborhood using the following concurrent strategies:

1 **Doctors’ offices**: Family doctors will be approached to help with recruitment. Healthcare professionals are in a unique position to identify individuals in need as they tend to be a point of contact for people who might not otherwise be interacting with other individuals and/or community services and who could benefit from greater physical activity, support for healthier eating, system navigation, and social engagement (67). Encouragement from healthcare professionals can also help leverage involvement in a program. Various study materials will be provided to doctor/clinic offices, with their prior approval (e.g., PowerPoint slides for offices with TVs, posters for waiting areas and individual rooms, pamphlets/handouts for interested individuals to take home and review).2 **Local communication channels**: Information on the study will be provided through established traditional media outlets (e.g., in local newspapers, community newsletters, radio, and television) and social media. While social media platforms may not directly reach all members of our older adult population, they may connect with agencies, family members and neighbors who could pass information on. All materials posted on communication channels will include a link to the flyer/poster for easy download/printing.3 **Posters**: Study posters will be placed in community sites such as grocery stores, pharmacies, multi-unit buildings, community information sites, recreation centers, places of worship and seniors’ centers. Recruitment materials will be translated into different languages to foster inclusive programming as needed.4 **Outreach services**: Older people who are socially isolated may be harder to recruit to the study. We will leverage existing services and supports to help reach this population, such as St Matthew’s House and Good Shepherd, two Hamilton-based community agencies providing support to older people experiencing food, housing or income security issues. These agencies also offer wellness programming and health system navigation. Staff may inform clients about EMBOLDEN and provide pamphlets when making porch visits/deliveries. Mail-ins to existing clients/members of community partner organizations by postal code is another strategy that may be employed.5 **Voice platform**: This project will also be advertised on the Voice platform, a community engagement platform that McMaster University’s Institute for Research on Aging (MIRA) is licensing from the University of Newcastle. The platform offers a place where researchers can work with community members through community engagement opportunities and posted research studies (with ethics approval). Members of the public find out about Voice and posted research studies either through directly accessing the website, or through emails the platform sends out of new opportunities to registered users. The research team receives names and contact information of interested participants from the Voice platform, and the Research Coordinator follows up to confirm inclusion criteria and provide more details about the study.6 **Direct mailings**: Directed mailings will be conducted if the above methods of recruitment do not secure enough participants. Direct delivery mailings through Canada Post to households in the targeted neighborhoods may be used. This recruitment strategy would be more costly and require a targeted approach so it will only be used if all other strategies are insufficient.^2^

All participants enrolled in the study, regardless of group allocation, will receive one $25 gift card for each quantitative data collection interview completed, for a maximum of three gift cards. This information is stated in all recruitment materials. Honoraria are provided to enhance recruitment by providing incentives to participate and mitigate attrition, particularly in the control group.

A cohort approach to recruitment and entry into the program will be adopted to foster socialization and relationship building (i.e., we aim to recruit all participants for a neighborhood to start within the first few weeks to allow intervention group participants opportunities to build relationships and socialize over the course of the program). One cohort will be rolled out per neighborhood with a maximum of 50 participants (25 intervention, 25 control) to be enrolled in each Hamilton (*n* = 8) and Toronto neighborhood (*n* = 2). Individual baseline data will be collected as individuals are enrolled in the study. The Research Coordinator will create monthly summary reports to enable the research team to determine whether recruitment targets are being met and whether additional targeted methods are needed to reach underserved groups. The final evaluation report will include the absolute number and percentage of individuals who responded to recruitment requests, enrolled, and retained in the program, as well as reasons for exclusion and dropout and comparison to the neighborhood characteristics collected through census data (see Table 1—RE-AIM outcomes and Table 2—Participant Timeline).

### Assignment of interventions

2.2

#### Allocation

2.2.1

The unit of randomization is the individual participant. The aim is to recruit 50 individuals in each neighborhood; these individuals will be randomized to receive the EMBOLDEN intervention versus usual care with a 1:1 ratio (25 individuals per trial arm at each site). The allocation process will use a randomized block design with three permuted block sizes (2, 4, 6). A biostatistician will generate the randomization sequence at each site using the *blockrand* package in R version 4.4.1.

#### Allocation concealment and implementation

2.2.2

The random number sequences for each site will be input into a central web-based service (REDCap®) that allocates participants to the two study arms in accordance with the sequence. Once the randomization sequences for each site are set up in REDCap, the system will be moved to production mode, which locks the randomization model, thereby ensuring that the sequence is not modified once the project begins. A Research Assistant will screen participants for eligibility and obtain consent from those who accept an invitation to participate (see Supplementary material for consent form). Once informed consent is obtained, the participant will be enrolled, baseline data will be collected, and the Research Coordinator will then obtain the participant’s group allocation from REDCap.

#### Blinding (masking)

2.2.3

Participants and interventionists will not be blinded. All data collectors will be independent of the intervention and blinded to treatment allocation. Statisticians will be blinded to treatment allocation.

### Data collection, management and analysis

2.3

#### Data collection methods

2.3.1

##### Smartwatch data

2.3.1.1

The watches are distributed to study participants in both groups by priority postal mail and returned to the research team through the same mechanism. Study participants in both groups (intervention, control) will be instructed to wear the smartwatch for 7 days prior to baseline (t_1_), and for the first 7 days of t_2_ (3 months) and t_3_ (6 months). Since the smartwatch is intended to collect objective data on physical mobility rather than serve as part of the intervention to incentivize/motivate it, all watches will be configured to allow participants to view only the time and not their activity data.

The checklist by Matthews et al. (68) will be used to ensure our design, implementation, and reporting are consistent with objective standards for the use of physical activity devices in population-based research. Table 3 provides our design and implementation decisions relating to the items in their checklist. We are primarily interested in the following mobility-related measures: heart rate (sampling rate: 1 Hz), accelerometer data (sampling rate: 50 Hz), and GPS data (sampling rate: upon movement or 5-min intervals).

**Table 3 tab3:** Checklist for design, collection and reporting of physical activity monitoring data.

Feature/characteristic	Criteria
Device Selection	The TicWatch Pro 3 Ultra GPS was selected to capture mobility-related data from participants. The primary reason for selecting this smartwatch over others was the ability to access the raw data. Raw mobility-related data of primary interest includes heart rate (sampling rate: 1 Hz), accelerometer data (sampling rate: 50 Hz), and GPS data (sampling rate: upon movement or 5 min intervals).
Reliability and validity of the device	The TicWatch Pro 3 Ultra GPS device is a high-quality smartwatch; its activity-related measures offer the reliability and validity of other smartwatches in its class (e.g., Fitbit, Garmin, Apple). (93)
Wearing location (on body)	Participants will be instructed to wear the watch on their non-dominant hand during waking hours and to charge the watch nightly.
Target sampling period	Participants will be instructed to wear the watch for 7 consecutive days prior to t_1_ (baseline), and for the first 7-days of t_2_ (3-months) and t_3_ (6-months).
Participant tracking method (wear time)	Wear time each day will be determined based on the number of heart rate observations for the day; this is a more reliable indicator of wear time compared to start/stop times for daily heart rate samples as there can be gaps during the day where no heart rate data are captured (e.g., due to no/low battery, participant remove watch for bathing/swimming). Examination of the smartwatch data collected in the pilot study showed that heart rate data was captured consistently in accordance with the developer’s specified sample frequency (1 Hz).
Quality control checks	Heart rate data will be checked for validity (i.e., no negative or 0 readings), and invalid data will be removed prior to analysis. Duplicate samples (i.e., samples having an identical time stamp) will also be removed. Based on the examination of the smartwatch data from the pilot study, very few invalid samples were found (e.g., <0.1% of the data). Step count data will be checked for reasonableness (e.g., unreasonably high values for target population) and obvious errors (e.g., negative numbers for step counts indicating an invalid reading). The smartwatch captures cumulative steps for the entire wear time for the time point (seven days for participants the comply with the protocol). Ending step counts for a given day will be matched with starting step counts for the next day, and discrepancies will be identified and appropriately resolved. Based on the examination of the smartwatch data collected in the pilot study, step counts were reasonable with no obvious errors. GPS data are challenging to validate, especially for this target population, many of which live in apartment dwellings where a GPS signal is often obstructed, and satellite coverage can be variable/unreliable. The level of accuracy (in meters) will be determined based on the distribution of the values, density for the study area, needed accuracy to distinguish between locations etc. Invalid data will be removed from the dataset prior to analysis.
Compliance criteria	For step count and GPS-related measures, all days with at least 6+ hours of wear time (up to a maximum of 7 days/participant/time point) available data will be used in the calculations (i.e., if participants only have data for 5 of the 7 days for a given time point, these days will be used to generate measures, including averages, distance measures, trips).
Summary variables/categorizing data	1) Heart rate data will be used to calculate the primary outcome (MVPA in minutes/day). Heart rate samples will be categorized as vigorous/moderate/light using the algorithms described in Section 2.1.5.1. 2) Step count data will be used to calculate a secondary outcome measure related to mobility. The TicWatch captures the total step count for each day the watch is worn. The average daily step count for each time point (t_1_, t_2_, t_3_) will be calculated by averaging across the wear period for each time point (seven days for participants that comply with the protocol). 3) GPS data will be used to calculate a variety of distance-related measures (e.g., number of trips, maximum distance from home, homestay ratio). The algorithms used to generate the measures using GPS data will be implemented in R version 4.4.1 and based on the R Markdown guidance document provided by Muller and colleagues (94).

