###### Primary outcome

2.1.5.1.1

The primary outcome is time spent doing moderate-to-vigorous physical activity (MVPA) measured in minutes/day at each of the three timepoints (t_1_ = baseline, t_2_ = 3-months, t_3_ = 6-months). This outcome was selected because physical mobility was a priority in the EMBOLDEN intervention based on co-design, funding agency priorities, and high-level evidence cites it as one of the most common measures used to evaluate the long-term effectiveness of physical activity interventions (34).

Mean minutes/day of MVPA at each timepoint will be estimated using heart-rate data captured by a smartwatch (TicWatch Pro 2 Ultra GPS), using two heart-rate-based equations:

1 Maximum heart rate (MaxHR): MaxHR will be estimated using a formula appropriate for older adults [207-(0.7xAge)] (35, 36), and samples will be classified as light, moderate or vigorous based on the following %MaxHR: very light/light (<64%), moderate (64–76%), vigorous (>76%) (37). The time spent with a heart rate in the moderate or vigorous zone will be calculated for each wear day in order to calculate an average min/day of MVPA for each timepoint.2 Heart rate reserve (HRR): also called the “Karvonen formula” (38, 39), this method uses %HRR to define physical activity intensity, where HRR = MaxHR – Resting HR (RestHR). MaxHR will be calculated as described above and RestHR will be calculated as the average of the daily minimum heart rate for 7 days. Samples will be classified as moderate/vigorous/light using the following formula: HRR × %Exertion, where moderate to vigorous intensity is % Exertion ≥40%. Samples in the moderate-vigorous categories will be aggregated and an average of minutes/day will be calculated for each timepoint as described above for MaxHR.

There is no clear guidance from the literature as to which approach is preferred, therefore, the change in the mean from baseline will be analyzed and reported for MVPA estimates from both algorithms.

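### The only smartwatch wear-time threshold covers step count and GPS; heart-rate MVPA, the primary outcome, is averaged over an undefined wear day

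*Protocol article*

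**What the plan says.** Section 2.3.1.1 (Smartwatch data) presents Table 3 as the trial's decisions on collecting and handling device data. The compliance row reads: "For step count and GPS-related measures, all days with at least 6+ hours of wear time (up to a maximum of 7 days/participant/time point"). When some days are lacking, "these days will be used to generate measures, including averages, distance measures, trips". No other row sets a threshold.

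The primary outcome uses a different signal: "Heart rate data will be used to calculate the primary outcome (MVPA in minutes/day"). Section 2.1.5.1.1 builds it in two ways:

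- **Percentage of maximum heart rate.** "The time spent with a heart rate in the moderate or vigorous zone will be calculated for each wear day". The daily totals are then reduced to one mean per visit.
- **Heart rate reserve.** "Samples in the moderate-vigorous categories will be aggregated and an average of minutes/day will be calculated for each timepoint as described above for MaxHR". This version also needs a resting heart rate: "RestHR will be calculated as the average of the daily minimum heart rate for 7 days".

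Daily wear is measured: "Wear time each day will be determined based on the number of heart rate observations for the day". The same row of Table 3 foresees gaps within a day from a flat battery or from taking the watch off to bathe. Quality control of heart rate removes only negative, zero and duplicate readings. The model in section 2.3.3.2 contains baseline value, arm, time, their interaction and random effects, with no wear-time term.

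**The concern.** A programmer following the text would drop days under 6 hours from the step and GPS measures and keep them for MVPA. The secondary outcomes would be protected and the primary would not.

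Minutes in zone are a total, so they depend on how long the watch was worn. A day with two hours of recording gives a small number of minutes and still adds one to the denominator. That number is an observed value. The mixed model's missing-at-random argument and the chained-equations imputation act only on missing values, so neither touches it. Adjusting for baseline MVPA removes only wear habits that are stable over time, not changes after allocation.

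At stake is the primary estimate, under both algorithms. Short wear at random shrinks the contrast and adds noise. Short wear that differs by arm shifts the contrast.

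**Working it through.** **No plan figure to reproduce.** The article prints no MVPA mean, SD or effect size, and the planned total of 250-500 is not in dispute here. The check is a comparison of text followed by an illustration.

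**Step 1, text.**

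| Rule | Step count, GPS (secondary) | Heart-rate MVPA (primary) |
|---|---|---|
| Minimum hours per day | 6 | none stated |
| Minimum valid days | none stated; all qualifying days used, up to 7 | none stated |
| Wear-time standardisation | none stated | none stated |

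**Step 2, effect on one participant.** Assumptions, none of them in the article: true MVPA M = 20 min/day, waking day W = 14 h, MVPA spread evenly over W. With k of 7 days worn for h hours and the rest worn fully:

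observed mean = [(7 - k) × M + k × M × h/W] / 7

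- k = 1, h = 2: (6 × 20 + 20 × 2/14)/7 = 122.86/7 = 17.55, a loss of 12.2%.
- k = 2, h = 2: (5 × 20 + 2 × 20 × 2/14)/7 = 105.71/7 = 15.10, a loss of 24.5%.

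The proportional loss is (k/7)(1 - h/W), which does not depend on M. For one short day it is 13.3% at h = 1, 11.2% at h = 3 and 8.2% at h = 6.

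**Step 3, sensitivity to the assumptions.** For one 2-hour day, W = 12 gives (1 - 2/12)/7 = 11.9% and W = 16 gives (1 - 2/16)/7 = 12.5%, so the length of the waking day matters little. Even accrual matters more. If all of that day's MVPA falls in the two recorded hours the loss is 0; if none does, it is 1/7 = 14.3%.

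**Step 4, equal wear by arm.** If participants in both arms average one 2-hour day in the follow-up week, unrelated to their activity, both arm means and their difference are multiplied by 1 - 0.122 = 0.878. Variation between participants in the number of short days adds variance.

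**Step 5, unequal wear by arm (hypothetical).** If the arms differ by δ in the mean number of 2-hour days per participant, the spurious difference is δ × M × (1 - 2/14)/7 = 0.1224 × δ × M. With δ = 0.5 this is 0.92, 1.84 and 3.67 min/day at M = 15, 30 and 60. Nothing in the article gives δ; it may be zero.

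**Step 6, how far a 6-hour rule goes.** Dropping the 2-hour days in Step 2 returns the mean to 20. A day worn for exactly 6 hours passes, yet records only 6/14 = 43% of the day's MVPA and still counts as one day. The threshold removes the worst days but does not make days comparable.

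**Step 7, resting heart rate.** The minimum over a few recorded hours can be no lower than the minimum over the full day containing them. One short day can therefore raise the averaged resting rate, and so shift the intensity cut-off for every sample in that week, including samples from fully worn days.

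**The case against.** **Silence is not a rule.** The article nowhere says that partly worn days count as full days. It is a condensed account, and a definition of a wear day could sit in the full protocol or an analysis plan. This stands in part: the behaviour described is what follows from averaging over an undefined unit, not a stated instruction. But the article does more than stay silent. It fixes a threshold and a scope, and the scope leaves out the primary outcome.

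**Bias between arms is conjecture.** This stands. Both arms get the same wear instructions, receive the watch by the same mail route and see only the time on the display. A reader might infer from section 2.1.8 that the plan expects poorer wear in controls, because honoraria are meant to limit attrition in that arm especially. The text does not support that. Attrition produces missing visits, not short days, and the honoraria are paid per completed interview, not for wearing the watch. Participants are unblinded (section 2.2.3), so different wear is possible, and no more than that.

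**Moderate wear differences are another matter.** A reader might blame the missing threshold for a contrast such as 13 against 11 hours of mean daily wear. If days lie near those means they all pass a 6-hour rule, so the distortion would remain. That example argues for wear-time standardisation, not for the threshold.

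**GPS measures.** A reader might also wish to divide maximum distance or convex-hull area by the number of valid days. Neither grows in proportion to days. The same 10 km² over 5 or 7 days would score 2.0 or 1.43 km²/day, rewarding shorter wear. The point here is confined to MVPA.

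**Conclusion.** The point holds for the primary outcome. The only printed wear threshold excludes it, and the averaging unit is undefined, so short-wear days enter as low observed values that the planned missing-data methods do not reach.

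Under the stated assumptions, one 2-hour day in seven costs about 12% of a participant's MVPA and two cost about 24%. These figures are nearly independent of the assumed waking hours, but they do rest on even accrual through the day.

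With equal wear by arm the consequence is attenuation and noise. A biased treatment contrast, in either direction, would need wear to differ after allocation, and the article gives no evidence that it does. It therefore does not support a claim that the trial is set up to show a false benefit. The gap still needs closing, because the primary estimate depends on it and the repair is cheap.

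**What to change.** Settle the following before any unblinded analysis; the blinded statisticians can do it from pooled wear data.

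1. Define a valid day for heart-rate MVPA: the existing 6-hour minimum or a stricter one. At 1 Hz, 6 hours is 6 × 3,600 = 21,600 heart-rate observations.
2. Apply it under both algorithms and to the days used for resting heart rate.
3. Set a minimum number of valid days per time point and treat time points below it as missing.
4. Report wear hours and valid days by arm and visit.
5. Because a 6-hour day still captures only about 43% of a 14-hour day, add a supporting analysis of MVPA standardised to wear time. State that follow-up wear is a post-randomisation variable, so this analysis supports the primary one and does not replace it.

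The cost is a few sentences and a few lines of code, since daily wear is already derived from heart-rate counts. The downside is that some visits become missing, on top of the planned 90% and 80% retention. The mixed model and multiple imputation then handle them under their missing-at-random assumption.
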